#### Walking/gait tasks.

Participants will choose from a selection of music tracks that span genres including pop, rock, R&B, and country. All walks will be 1-minute in duration in a continuous 25m loop, including two 8.5m straight segments and two 4m turns, Fig 3. Walk #1 will be at the participant’s natural walking pace to calculate a baseline cadence, i.e., a walk with no cueing (NC). Walks #2, #4, and #6 will be cued, with external auditory stimuli (BPM set at +10% of baseline cadence) which are metronome (Me), instrumental music (IM), and vocal music (VM). Participants will be assigned to one of three counterbalanced cue sequences for Walks #2, #4, and #6. For example, the first participant enrolled to the study follows Sequence 1, the second follows Sequence 2, the third follows Sequence 3, and the fourth cycles back to Sequence 1, etc.

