**Fig 3 pone.0346508.g003:**
[figure not shown]
25m walking loop consisting of two straight and two curve sections.

Following Walks #2 and #4, a two-part washout (WO1 and WO2) will be implemented to minimise any potential carryover effects from the previous auditory cue. Part 1 (of WO1 and WO2) will involve participants sitting and counting backwards in their heads from 30 to 0 in increments of 1 to disengage any psychological responses triggered by the cueing modality [72]. Part 2 (of WO1 and WO2) will consist of a 1-minute walk at the participant’s natural pace, to further reset their gait but also to assess whether any carryover effect remains before the next cue begins. This approach ensures each cue’s effects are evaluated independently of preceding sequences:

Sequence 1–20 participants: NC, Me, WO1, IM, WO2, and VM.Sequence 2–20 participants: NC, IM, WO1, VM, WO2, and Me.Sequence 3–20 participants: NC, VM, WO1, Me, WO2, and IM.

Accordingly, the complete sequence consists of (Fig 4):

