#### Sample size.

Sample size calculations were based on detecting changes in gait speed using a within-subject design. Assuming a standardised response mean (SRM) of 0.5 (moderate effect size) for gait speed, a two-sided significance level (α) of 0.01, and 90% power, approximately 54 participants would be required to detect a statistically significant change in gait speed for a single comparison (e.g., cued vs. non-cued walking). When accounting for the three cueing conditions and the associated adjustment for multiple (three) comparisons, we applied a Bonferroni correction resulting in an adjusted alpha of α (0.01/3 = 0.0033). That requirement increases sample size to approx. 55 participants. However, to allow for an anticipated attrition rate of up to 10%, we plan to recruit 60 participants in total. This sample size ensures adequate power to detect moderate cueing effects on gait speed, accommodates potential dropouts, and provides balanced representation across randomisation sequences.

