If assumptions for normality are not met, a Friedman test will be used to assess within-subject differences across cueing conditions. Post-hoc Wilcoxon signed-rank tests, with Bonferroni correction, will be conducted only if the Friedman test is statistically significant. For between-subject effects (e.g., walk order), where normality assumptions are violated, the Kruskal–Wallis test will be used to assess group-level differences between walk-order groups. Interaction effects between cueing and walk order will be explored non-parametrically by conducting separate Friedman tests within each walk order group. Effect sizes for non-parametric tests will be calculated using the rank-biserial correlation coefficient, $\text{r}=\text{Z}/\sqrt{\text{N}}$, providing a measure of the magnitude of the effects observed.

For the three primary comparisons, we will control the familywise error rate using a Bonferroni adjustment. Given three cueing modalities, statistical significance (*p*) will be evaluated at a two-sided α = 0.01/3 = 0.0033. Effect sizes (i.e., SRM) and 95% confidence intervals will also be reported. Secondary and exploratory analyses (e.g., comparing cueing modalities to one another, examining washout effects, assessing stride-to-stride variability) will not be subject to multiplicity correction. For these analyses, a two-sided *p*-value of 0.05 will be considered statistically significant across all parametric and nonparametric tests.

To assess whether the first cue produced short-term residual effects, we will calculate changes in gait outcomes from baseline to each cued walk and from each cued walk to its subsequent washout walk (WO1 and WO2). For each cue exposure, a carryover score will be calculated as the difference between the change induced by the cue and the change observed during the corresponding washout period, reflecting retained cue effects. The approach enables an evaluation of carryover effects after each cued walk separately, thereby capturing any cumulative or progressive retention of cueing effects. Group differences based on initial cue type (i.e., counterbalanced sequence) will be evaluated using one-way ANOVA or the Kruskal–Wallis test, depending on normality assumptions [74–80].

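### The three cue sequences balance position but not the preceding cue and are allocated by rotation, so the design cannot guarantee independence from earlier cues; the per-sequence Friedman fallback confounds cue with walk position

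*Protocol article*

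**What the plan says.** The section on walking/gait tasks says "Participants will be assigned to one of three counterbalanced cue sequences for Walks #2, #4, and #6". Allocation follows enrolment order: "the first participant enrolled to the study follows Sequence 1, the second follows Sequence 2, the third follows Sequence 3", and the fourth participant returns to Sequence 1. The sequences are:

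- Sequence 1: "20 participants: NC, Me, WO1, IM, WO2, and VM"
- Sequence 2: "20 participants: NC, IM, WO1, VM, WO2, and Me"
- Sequence 3: "20 participants: NC, VM, WO1, Me, WO2, and IM"

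Between cued walks there is a washout: a seated silent count from 30 to 0, then a 1-minute uncued walk. The same section says this ensures that each cue's "effects are evaluated independently of preceding sequences". The sample-size section says the chosen N "provides balanced representation across randomisation sequences".

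The statistical analysis section models cue as a within-subject factor and walk order as a between-subject factor. It derives carryover scores from the washout walks and compares them by initial cue. If normality fails, it explores the cue-by-order interaction by "conducting separate Friedman tests within each walk order group".

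**The concern.** Three sequences suffice to put every cue in every position, but not to have every cue preceded equally often by each of the others. If a cue leaves something behind after the washout, all of it falls on one particular other cue. The trial also aims, under the heading on the impact of cueing, to identify which cues work best, and that comparison is the one most exposed to unequal residuals.

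Three further statements do not fit the design. The guarantee of independence is stronger than a short washout and an unbalanced order can support. A rotation by enrolment order is not randomisation: staff can foresee the next sequence, which weakens comparisons between sequence groups. And within a single sequence every participant meets the cues in the same order, so a test confined to that sequence would read fatigue or practice as a cue effect.

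**Working it through.** **Inputs.** Three sequences of 20 (walking/gait tasks), so 3 × 20 = 60, which agrees with the planned total under Participants. Rotating 60 people over three sequences gives the stated 20 each.

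**Position and precedence**, counted from the listed sequences (Me metronome, IM instrumental, VM vocal):

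| Cue | In each of positions 1, 2, 3 | First, no earlier cue | After its fixed predecessor | After the other cue |
|---|---|---|---|---|
| Me | 20, 20, 20 | 20 | 40 (VM) | 0 (IM) |
| IM | 20, 20, 20 | 20 | 40 (Me) | 0 (VM) |
| VM | 20, 20, 20 | 20 | 40 (IM) | 0 (Me) |

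**Bias.** Let L_Me, L_IM and L_VM be the residuals each cue leaves on the next cued walk (first-order carryover only). The documents give no values. The mean of a cue shifts by (40/60) × its predecessor's residual:

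- IM by 2L_Me/3, VM by 2L_IM/3, Me by 2L_VM/3.
- IM − VM is therefore biased by (2/3)(L_Me − L_IM), and the other contrasts follow the same pattern.

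Illustrations with assumed residuals, in points of the outcome:

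- Me leaves 3, the others 0: IM − VM is off by (2/3) × 3 = 2.
- Residuals 3, 2, 2 for Me, IM, VM: (2/3) × (3 − 2) = 0.67.
- Residuals 3, 3, 3: zero bias in every between-cue contrast, but each cued-versus-baseline change is shifted by (2/3) × 3 = 2.

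With all six orders at 10 each, every ordered pair occurs 20 times. A residual L from one cue then shifts each of the other two means by L/3 instead of one mean by 2L/3.

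**Cost of adjusting for carryover.** Least squares with participant, period and cue effects, N = 60. Entries are the variance of a cue contrast in units of the residual variance.

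| Walks used | Design | Without carryover | With carryover | Ratio |
|---|---|---|---|---|
| Three cued walks | Three cyclic orders | 0.0333 | 0.1667 | 5.0 |
| Three cued walks | Six orders | 0.0333 | 0.0417 | 1.25 |
| All six walks | Three cyclic orders | 0.0333 | 0.0556 | 1.67 |
| All six walks | Six orders | 0.0333 | 0.0370 | 1.11 |

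The six-walk rows assume that a washout walk and the cued walk after it carry the same residual.

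**Planned carryover comparison.** Grouping by initial cue is the same as grouping by whole sequence, so this comparison cannot separate a cue from its fixed predecessor.

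**Per-sequence Friedman tests.** Within one sequence, cue and position are one variable. Simulation with no cue effect: 20 per sequence, independent normal errors, a linear trend per cued walk in units of the error SD, two-sided 0.05, 4000 runs.

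| Assumed trend per cued walk | Each test rejects | At least one of three rejects |
|---|---|---|
| 0.25 SD | about 20% | about 49% |
| 0.5 SD | about 65% | about 96% |

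Setting three separate p-values side by side does not test whether the cue effect differs between orders.

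**The case against.** The strongest reply has five parts.

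- **Carryover is unproven.** There is a washout, and each cue comes first, with no earlier cue, for 20 of 60 participants. This stands: the documents support saying that independence is not guaranteed, not that it fails.
- **Similar residuals are plausible.** All cues run at the same +10% of baseline cadence, and equal residuals cancel in between-cue contrasts. This stands for those contrasts, but not for the cued-versus-baseline changes. Nor would six orders remove all bias: a residual L from metronome alone would leave L/3 in both IM − Me and VM − Me, and VM − Me has none under the current sequences.
- **The factor of 5.0 ignores data the trial collects.** With the baseline and washout walks it falls to about 1.67, under the shared-residual assumption. This stands.
- **Between-cue comparisons are secondary.** The statistical analysis section says so, and the Discussion disclaims definitive superiority of one cue, reading responses as conditional on sequence. This limits the consequence. It also sits badly with the guarantee of independence, and a caveat removes no bias.
- **The Friedman tests are an exploratory fallback.** They apply only if normality fails, and the rejection rates rest on assumed trends. That is so, but the confounding of cue with position holds whatever the trend, and six orders would not cure it.

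A reader might also infer that the trial is presented throughout as randomised. The documents do not support that: the term appears once, in the sample-size section, while elsewhere participants are assigned or allocated. It is one inconsistent term.

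**Conclusion.** The point holds as a limit on what the design can guarantee. Position is balanced and precedence is not: 40 occurrences of each of three ordered cue pairs, none of the reverse pairs. The allocation is a foreseeable rotation. Because every participant receives every cue, foreseeability mainly affects comparisons between sequence groups.

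If residuals are unequal, secondary between-cue contrasts are biased by two thirds of the difference between the residuals concerned. If they are equal, only the cued-versus-baseline changes shift. The size of L is unknown, and all of this assumes first-order carryover. Adjustment is possible, at a variance cost between about 1.67 and 5.0 times depending on whether the baseline and washout walks are used.

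It would be tempting to conclude that the cue effects are contaminated or that the primary comparisons are invalid. Nothing in the documents shows that carryover survives the washout, so neither follows.

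The Friedman fallback is a separate fault and is wrong as written.

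**What to change.** 1. In the walking/gait tasks section, replace the guarantee with a statement that the washout aims to reduce carryover and that the preceding cue is not balanced.
2. In the sample-size section, call the allocation rotation by enrolment order.
3. Replace the per-sequence Friedman tests with one model across all sequences with participant, cue and walk position, on transformed or ranked data if normality fails.
4. Add a sensitivity analysis with a preceding-cue term that uses the washout walks, stating the shared-residual assumption.
5. Add a sensitivity analysis of Walk #2 only, first cue against baseline. No cue comes before it, but with about 20 participants per cue it is imprecise.
6. Only for participants still to be enrolled, if any, use all six orders from a concealed random list. The stated recruitment window, September 2024 to December 2025, may leave few or none.

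Items 1 to 5 need no new data: a few sentences and slightly more analysis. Item 6 would create two allocation phases with unequal sequence groups, which the analysis would have to report.

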**Fig 3 pone.0346508.g003:**
[figure not shown]
25m walking loop consisting of two straight and two curve sections.

Following Walks #2 and #4, a two-part washout (WO1 and WO2) will be implemented to minimise any potential carryover effects from the previous auditory cue. Part 1 (of WO1 and WO2) will involve participants sitting and counting backwards in their heads from 30 to 0 in increments of 1 to disengage any psychological responses triggered by the cueing modality [72]. Part 2 (of WO1 and WO2) will consist of a 1-minute walk at the participant’s natural pace, to further reset their gait but also to assess whether any carryover effect remains before the next cue begins. This approach ensures each cue’s effects are evaluated independently of preceding sequences:

Sequence 1–20 participants: NC, Me, WO1, IM, WO2, and VM.Sequence 2–20 participants: NC, IM, WO1, VM, WO2, and Me.Sequence 3–20 participants: NC, VM, WO1, Me, WO2, and IM.

Accordingly, the complete sequence consists of (Fig 4):

**Fig 4 pone.0346508.g004:**
[figure not shown]
A diagrammatic representation of the study sequence.

(i)
**Baseline walk (walk #1):**
aThe participant navigates a 25m flat surface loop at a natural/self-selected pace for 1-minute. Baseline cadence is determined.(ii)
**Cued walks (walks #2, #4, and #6 cue sequence varies by participant, as above)**
b
**Walk #2:**
iThe participant navigates the same 25m loop while allocated to a sequence (above) set at +10% of their baseline cadence (walk #1).iiInstructions to the participant: Walk to the beat of the cue.iiiWO1 (Part 1: sitting and counting backwards followed by Part 2: 1-minute walk at self-selected pace)c
**Walk #4:**
ivThe participant navigates the same 25m loop while allocated to a sequence (above) set at +10% of the baseline cadence.vInstructions to the participant: Walk to the beat of the cue.viWO2 (Part 1: sitting and counting backwards followed by Part 2: 1-minute walk at self-selected pace)d
**Walk #6:**
viiThe participant navigates the same 25m loop while allocated to a sequence (above) set at +10% of baseline cadence.viiiInstructions to the participant: Walk to the beat of the cue.

### Outcome measures

#### Validation of gait characteristics.

This assesses the validity of CuePD to quantify PwPD gait characteristics against an established gold/reference-standard wearable (Opal). Gait characteristics include the mean, variability and asymmetry of temporal, spatial, and spatiotemporal characteristics (i.e., step time, stride time, stance time, swing time, stride length). Establishing the validity of CuePD in measuring gait characteristics is essential to accurately detect changes before and after cueing and to precisely tailor the administered cues to each individual’s physiological condition.

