#### Reference standard.

The reference for this study is Opal (https://clario.com/solutions/precision-motion-for-research/) which interfaces with Mobility Lab, a validated commercially available system that enables comprehensive gait assessment [22]. It allows for the wireless synchronisation of up to six IMUs (Opal V1), which incorporate tri-axial accelerometers (range:  ±  16g and  ±  200g), gyroscopes (range:  ±  2000°/s), and magnetometers (range:  ±  8 Gauss). During each walking task, a single Opal IMU (26g, 50 × 40 × 14 mm), sampling data at 128 Hertz/Hz, will be attached to the talus joint of each foot of the participant. Reference standard data will be used to validate CuePD’s temporal, spatial, and spatiotemporal gait characteristics (inc. asymmetry and variation) in PwPD to ensure primary outcomes are robust.

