### Statistical analysis

For the first primary objective, all gait characteristics derived from CuePD and reference will be compared using ICC_2,1_ (absolute agreement), a two-way random-effects model for single measures that evaluate the absolute agreement between raters. The level of agreement will be interpreted as: < 0.5 shows poor agreement, 0.5–0.75 moderate, 0.75–0.9 good and 0.9–1.0 excellent. PCC’s will be calculated to measure the linear correlation between the two sets of results. Correlation coefficients will be interpreted as follows: zero (0), weak (±0.1 to ±0.3), moderate (±0.4 to ±0.6), strong (±0.7 to ±0.9), and excellent/perfect (+1 or −1).

The median, mean, standard deviation (SD), minimum/min, maximum/max, and standardised response mean (SRM) of cadence, stride length, gait speed and CV_stride-time_ will be calculated. These descriptive statistics will provide context for interpreting changes and help to clarify the magnitude and consistency of cueing effects. SRM allows for assessment of responsiveness and comparison of results to other studies. The SRM will be interpreted as: > 0.8 large positive response, 0.5–0.8 moderate responsiveness, and <0.5 low responsiveness where positive values imply an improvement for cadence, gait speed and stride length but negative is an improvement for CV_stride-time_, i.e., reduces variability.

To evaluate the cueing modality adherence, the percentage change in cadence from the baseline walk to each cueing modality will be calculated for each participant. The most effective cueing modality will be identified as the one producing a change closest to 10%.

Model assumptions will be formally checked, where residual normality and normality of gait characteristics within each cue condition will be assessed using the Shapiro-Wilk test, and sphericity with Mauchly’s test. The Greenhouse-Geisser correction will be applied if sphericity is violated.

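### The validation list omits gait speed and cadence, and agreement is planned on walk values but not on the change from baseline that the validation is meant to support

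*Protocol article*

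**What the plan says.** **What is validated.** Under Outcome measures, Validation of gait characteristics, the article announces means, variability and asymmetry of temporal, spatial and spatiotemporal characteristics, and spells these out as "i.e., step time, stride time, stance time, swing time, stride length". That is four times and one length. The same paragraph states the purpose: "Establishing the validity of CuePD in measuring gait characteristics is essential to accurately detect changes before and after cueing".

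**How.** Under Statistical analysis, "all gait characteristics derived from CuePD and reference will be compared using ICC_2,1_ (absolute agreement" form), on a scale where below 0.5 is poor, 0.5–0.75 moderate, 0.75–0.9 good and 0.9–1.0 excellent. In addition, "PCC’s will be calculated to measure the linear correlation between the two sets of results". No agreement analysis of change from baseline is stated.

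**What the cueing objective uses.** The Sample size section says: "Sample size calculations were based on detecting changes in gait speed using a within-subject design". The mixed ANOVA takes cadence, gait speed, stride length and stride-time CV as outcomes, and the section describes them as within-participant changes from baseline. Cadence also fixes the cue tempo (baseline plus 10%) and defines adherence (a rise of at least 5%).

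**The reference device.** The Reference standard section has an Opal sensor on each foot during each walking task, and says its data will validate CuePD "to ensure primary outcomes are robust". The article does not state which device supplies the values for the cueing analysis.

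**The concern.** There are two linked problems.

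First, the list does not match the rest of the article. Read as written, it leaves out the outcome on which the trial is sized and the outcome that drives both the cue and the adherence definition. It contains no spatiotemporal item, although the sentence promises some. The Discussion, under the primary objectives, speaks of establishing the validity of stride length, gait speed and stride-time CV as measured by the app.

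Second, the statistics do not reach the stated purpose. A level ICC compares device error with the spread between people. That spread cancels in a cue-minus-baseline difference, while error that is independent between walks adds up. Pearson correlation does not register bias, and neither statistic gives error in gait units.

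At stake is interpretation. The abstract promises to keep measurement performance apart from behavioural effects. If cueing outcomes come from the app and the effect looks small, the planned validation may not tell whether cueing did little or the app tracked change poorly.

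**Working it through.** The plan gives no numerical figure for the validation objective, so there is none to reproduce. The check has two parts.

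**1. The sections side by side**

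| Section | Gait speed | Cadence |
|---|---|---|
| Validation of gait characteristics (list) | not named | not named |
| Statistical analysis, validation | only if covered by the word all | only if covered by the word all |
| Sample size | basis of the calculation | – |
| Statistical analysis, ANOVA | outcome | outcome |
| Smartphone and CuePD; Walking/gait tasks | – | sets cue tempo |
| Adherence to cues and musicality | – | defines adherence |
| Discussion, primary objectives | validity promised | – |

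**2. Level agreement against change agreement**

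The documents give no device-error or between-person figures. All standard deviations (SDs) below are assumptions, in m/s for gait speed.

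*(a) Equal error in both devices, independent between walks.* With between-person SD s_b, SD of true change s_d and error SD s_e in each device:
- level ICC = s_b² / (s_b² + s_e²)
- change ICC = s_d² / (s_d² + 2s_e²)

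s_b = 0.20, s_d = 0.08, s_e = 0.07: level 0.04/(0.04 + 0.0049) = 0.89 (good); change 0.0064/(0.0064 + 0.0098) = 0.40 (poor).

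s_b = 0.20, s_d = 0.10, s_e = 0.05: level 0.04/(0.04 + 0.0025) = 0.94 (excellent); change 0.01/(0.01 + 0.005) = 0.67 (moderate).

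*(b) Level ICC held at about 0.95, error in the app only.* Take s_e² = s_b²/9, so the baseline ICC is s_b²/(s_b² + s_e²/2) = 1/(1 + 1/18) = 0.947. Let s_b be 0.15 to 0.25 and mean true change 0.03 to 0.08, with s_d twice the mean so that the true standardised response mean (SRM) is the planned 0.5.

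- Error independent between walks: change ICC = s_d²/(s_d² + s_e²). Lowest (s_b = 0.25, mean 0.03): 0.0036/(0.0036 + 0.00694) = 0.34. Highest (s_b = 0.15, mean 0.08): 0.0256/(0.0256 + 0.0025) = 0.91.
- SRM seen through the app = mean/√(s_d² + 2s_e²): from 0.03/√(0.0036 + 0.01389) = 0.23 to 0.08/√(0.0256 + 0.005) = 0.46, against 0.50.
- Power with 60 participants at two-sided 0.0033 (exact paired t): 11% to 68%, against 79% at SRM 0.5. That 79% is below the planned 90% is a separate matter and not needed here.
- Error constant within a person: it cancels in the difference. Change ICC is 1.00 and the SRM is unchanged.

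*(c) App without random error that records only half of the true change.* The ICC in the cued walk is still 0.90 to 0.99 over the same grid, while the mean change in m/s is halved. The change ICC is 0.76 and the SRM stays at 0.50, so only the mean bias shows the problem directly.

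A high level ICC is therefore compatible with poor, moderate or excellent agreement on change.

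**The case against.** The case on the other side has real weight.

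- **Wording.** "all gait characteristics derived from CuePD and reference will be compared using" the ICC can be read to include gait speed and cadence, and the outcome paragraph itself announces spatiotemporal measures. The omission may be loose drafting. This stands in part: it makes the point one of reconciliation, but the list is introduced by i.e. and as written it is closed.
- **Derived quantities.** Mean cadence is nearly the reciprocal of mean step time, so that omission is mild. Gait speed is roughly stride length over stride time, but it combines the errors of both, so their separate ICCs do not settle it.
- **The statistics.** ICC(2,1) is the absolute-agreement form and does penalise bias; Pearson correlation is supplementary. True, but this concerns walk values. Condensed articles often leave extra agreement statistics to a fuller plan. Here, however, the article fixes both the purpose and the methods, and the methods do not serve the purpose.
- **Error structure.** All walks form one sequence with the same attachment sites, so part of the error may be constant within a person and cancel. This stands, and the documents do not say how large that part is. The planned SRM of 0.5 may also already include measurement noise, in which case the power loss above would be overstated.

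A reader might infer that the app's change scores are mostly measurement error, or that the validation is bound to fail. The documents do not support that: it needs large, independent error, and no error figure is given. Nor do they support insisting that Opal be the primary data source. The article does not name the source, and using app values could be deliberate in a study of the app.

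**Conclusion.** The point holds in limited form. The list conflicts with the Reference standard, Sample size, Statistical analysis and Discussion sections and needs reconciling, chiefly for gait speed. The stated agreement statistics do not by themselves establish that the app detects change, which is the declared purpose of validation.

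The size cannot be fixed from the documents. At a level ICC of about 0.95, agreement on change could lie from poor (0.34) to perfect (1.00), depending on how far device error is constant within a person and on the assumed spreads. Independent zero-mean error leaves the mean change unbiased. It lowers the SRM and power and would not create a cueing effect. Proportional under-recording of change would bias the estimated effect in gait units towards zero. The trial remains runnable; one of its two primary objectives would deliver less than the article claims for it.

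**What to change.** 1. In Validation of gait characteristics, add gait speed and, less critically, cadence to the list, so that it agrees with the other sections.
2. In Statistical analysis, for each cueing outcome (cadence, gait speed, stride length, stride-time CV), report mean bias and 95% limits of agreement beside the ICC. Do this for walk values and for each cue-minus-baseline change, with one pair per participant per walk or per change.
3. State which device supplies the values for the cueing analysis, and report the cueing effect from the other device as a sensitivity analysis.

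The cost is a little more analysis. Because the Opal sensors are worn in every walking task, no new data, visits or participants are needed.
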